## Abstract

**Introduction:**

Assistance provided to support people living with dementia and carers is highly valued by them. However, current support systems in Australia are disjointed, inaccessible to all, poorly coordinated, and focus on dysfunction rather than ability. Support workers for people with dementia are in short supply, and there is little consistency in their roles. To address this large service gap and unmet need, we have developed an evidence-based optimized model of holistic support for people with dementia and their carers and families. This article describes the “*Support for Life*” model intervention.

**Methods:**

A stepped wedge cluster randomized controlled trial will be conducted over 3 years across three Australian states. One hundred participants with dementia and/or their carers/family members will be randomly selected from community health center client lists in each state to receive either the dementia “*Support for Life*” intervention (Group A) or routine care (Group B). Group A participants will have access to the intervention from year 1. Group B participants will continue to receive usual care and will not be denied information on dementia or dementia services in year 1. In year 2, Group B participants will have access to the intervention. A highly trained expert dementia support worker will provide the “*Support for Life*” intervention, which is a flexible, individually tailored, holistic support that is relationship-centered, focused on enablement as opposed to dysfunction, and facilitate participants’ continued engagement in their community and the workforce. Additionally, dementia education, information resources, advocacy, and practical support to navigate and access dementia services and health care will be provided. The mode of support will include face to face, telephone, and internet interaction on an “as needed basis” for 12 months. The primary hypothesis is that the intervention will improve the quality of life of people with dementia and the health and well-being of carers/family through facilitating the continuation and enhancement of regular daily activities. Secondary hypotheses will examine other health and service usage outcomes. The outputs will also include a health economic analysis to investigate the costs (and savings) of any associated reduction in unnecessary health services use and delay in accessing permanent residential aged care.

**Trial registration number:**

Australian and New Zealand Clinical Trials Registry: ACTRN12616000927426p.

## Introduction: Background and Rationale

Models of support to assist people with dementia and their carers to adjust to living with memory loss, to navigate the health and aged care system, and to access services, information, and support have recently been implemented both in Australia and overseas. However, there has been little high level evaluation of these services prior to a recent project that evaluated the effectiveness of the support worker role through a systematic review of international literature of support workers and models of support workers operating across Australia (1, 2). This study was undertaken by members of the National Health and Medical Research Center (NHMRC) Cognitive Decline Partnership Center (CDPC) using a codesign approach involving consumers, industry partners, policy makers, and researchers to ensure a wide range of perspectives, including those of people with dementia, carer’s, and those working in the aged care industry (1, 2).

Findings from the CDPC project demonstrated that, although the dementia support worker role is highly valued, the current support system for people with dementia, their carers, and families is based on a biomedical model, is disjointed, poorly coordinated, and focuses on dysfunction and not on what people with dementia can still achieve. Additionally, no one service delivery model is accessible for people of all ages, diverse needs, or geographic locations. Our results also revealed insufficient numbers of support workers, support workers having high case loads that lead to them being time poor and experiencing burn out, and a lack of appropriate services available in the community to assist people with dementia and their families and carers to continue to undertake many of the regular activities of their daily life or actively engage in their community (2). Differences in available services were also dependent on the location of the service, such as the state in which the service was located and whether it was in a rural or metropolitan area (2). To address these gaps in services and the unmet needs of people with dementia and their carers and families, we have used the results from a systematic review of international models of support workers, an evaluation of Australian key worker models, and the perspectives of people with dementia and their carers to develop an optimized evidence-based support model (1–3).

Our evidence-based optimized dementia support worker model “*Support for Life*” is underpinned by an overarching philosophy that incorporates the four key themes: relationship-centered, enablement, holistic, and accessible. It articulates three components necessary to address current shortcomings: the necessary organizational context in which dementia support workers are able to operate autonomously, the definition of the role and what activities a dementia support worker role undertakes, and the competencies that are required to carry out the role successfully (2).

As no previous Australian studies have demonstrated, high level evidence of the efficacy of a consumer-directed dementia support worker model that focuses on enablement and meeting the individual needs of people with dementia and their carers/family members, we propose to test the efficacy of our optimized dementia support worker model by way of a cluster stepped wedge randomized controlled trial (4, 5).

This cluster stepped wedge randomized controlled trial will be the first Australian study to measure the efficacy and cost-effectiveness of the dementia support worker model. It is anticipated that this trial will provide high quality evidence of the efficacy and cost-effectiveness of a tailored, holistic, flexible, single service, and consistent approach to supporting people with dementia and their families and carers that promotes their well-being through the integration of services and health care, provision of emotional support, and enabling/encouraging them to remain actively engaged in the community.

### Explanation for Choice of Comparators

The design was developed to combine the rigor of a cluster randomized trial with the pragmatic approach of the stepped wedge design to implement the intervention at all sites (4–6).

### Objectives

To trial an optimized model, the “*Support for life*” program, based on the findings from the NHMRC CDPC evaluation that investigated the provision of support to people with dementia and their carers to address current shortcomings in support for people with dementia and their carers/families.

The “*Support for Life*” trial will be undertaken by a multidisciplinary team with extensive track records in all key areas of the project. This team combines expertise in dementia knowledge, translation knowledge, provision of support, and delivery of health services to people experiencing memory problems, cognitive impairment, or dementia; and research methods including randomized controlled trials (RCTs). The team will also have access to expert health economic, policy and research design through the CDPC enabling subunits, consumers and consumer representation through the Alzheimer’s Australia Consumer Dementia Research Network (CDRN) and statistical advice from the RDNS Institute statistician.

The “*Support for Life*” program is a whole of family approach to support that will assist people with dementia, their carers, and families to identify services that meet their individual need and offer them greater control and choice to continue to live and engage in life as fully as possible. This will help ensure that these services/supports include opportunities for people with dementia to have full access to “life activities” such as employment and recreation. Support will also focus on providing family members and/or carers the ability to actively participate in society and not be disadvantaged by their caring role. Active participation may mean continuing to work, attend school, university, and receiving appropriate support in these environments. To adhere to the overarching relationship-centered, enablement, holistic, and accessible principles that underpin the “*Support for Life*” program, workers providing support to people with dementia and their carers/families will
require competencies in dementia knowledge, communication and interpersonal skills, the ability to generate ideas and problem solve, build and maintain relationships, and be empathetic and a good listener (1, 2).be enabled by a model of organizational support, which will ensure flexibility and autonomy, adequate resources, infrastructure and personal support, quality assurance practices, and facilitate appropriate inter-professional and inter-sectoral collaboration (1, 2).have a clearly defined description of the role that incorporates the flexibility and autonomy to refer and link to services, assist with navigation of the service system, act as a point of contact and advocate, respond to individual needs, provide dementia-related education and information, provide practical and emotional support (1, 2).

### Hypotheses

We hypothesize that connecting people with dementia and their families and carers to dementia support workers and volunteer mentors will lead to improvements in quality of life, reduce symptoms of depression, and facilitate the continuation of regular daily activities and enable community participation. The primary hypotheses are that involvement in the “*Support for life*” intervention will
improve the quality of life of people with dementia in the intervention group compared with the control group.improve the health and well-being of carers and/or family members in the intervention group compared with the control group.

The secondary hypotheses are that the involvement in the “*Support for Life*” intervention will
reduce depression experienced by people with dementia in the intervention group compared with the control group.reduce the utilization of health-care resources by people with dementia in the intervention group compared with the control group.lead to an increase in uptake of support/respite services/engagement in activities by people with dementia in the intervention group compared with the control group.lead to a delay in accessing permanent residential aged care by people with dementia in the intervention group compared with the control group.reduce depression/psychological distress experienced by carers and/or family members in the intervention group compared with the control group.

### Trial Design

The evaluation of the “*Support for Life*” complex intervention will occur within a step-wedge cluster Randomized Controlled Trial (cRCT) involving multiple community health centers across three states over 3 years. Clusters are the community health centers, and approximately 10 centers in each state will participate in this study. Half of the centers (Group A) will be randomized to receive the intervention in year 1 and the other half in year 2 (Group B).

This “*Support for Life*” complex intervention proposes to trial a framework of a single service, highly flexible holistic approach to support for people with dementia and their families/carers. It will provide a platform to integrate current services and health care, provide emotional support, and enhance community and social engagement. Important principles are
Protecting the person with dementia and their rights to full citizenship regardless of their age, gender, and cultural background.Providing access to support where there is diminished decision-making capacity, retaining respect for the person with dementia but also the advocating for the rights of the family and caring unit.Improving access to palliation and “end of life care” in the setting of advanced or impaired decision-making, including with those who live alone.

This type of response builds on the strengths in a caring unit and addresses the needs of individual relationships. In line with “codesign” and “consumer directed care” (CDC) principles, the person with dementia, their family, and other members of the caring unit will actively design/influence what this service response will look like. Ongoing evaluation will allow for flexibility and change.

## Methods: Participants, Interventions, and Outcomes

### Study Setting

#### Community/Primary/Ambulatory Care

Collaborations with Primary Health Networks (PHNs) in Victoria, New South Wales, and Queensland will be used to assist with the identification of community health centers from metropolitan and regional areas, have a high incidence of patients with dementia, and diverse populations (including CALD and LGBTI).

### Eligibility Criteria

Criteria for inclusion will include people who are experiencing memory problems, cognitive decline, or having a formal diagnosis of dementia who are living in the community setting and willing to provide written, informed consent to participate in the study. People who are unable to self-manage but who have a carer will not be excluded from the study. Carers and family members of a person who is experiencing memory problems, cognitive decline, or dementia and are willing to provide written, informed consent are also eligible for participation in the study. The exclusion criteria include consumers who are already receiving a support intervention or have acute psychosis.

### Intervention

Dementia Support Workers, recruited from each of the three states, will inform the Community Health Centers of our trial of the provision of dementia friendly support to their patients by assisting them in getting the right services and the right people at the right place.

Group A participants will be from Group A cluster sites and will have access to the “*Support for Life*” intervention from year 1. This “*Support for Life*” complex intervention proposes to trial a framework of a single service, highly flexible holistic approach to support for people with dementia and their families/carers. It will provide a platform to integrate current services and health care, provide emotional support, and enhance community and social engagement by
Working with the “person with dementia or cognitive impairment and those who support them” regardless of age, gender, and cultural background.Focusing on strengths of the people involved in order to maintain and improve physical and emotional health and well-being.Planning for the future to provide peace of mind.Use of an assistant and volunteers to help identify/create/facilitate access to services and enhance the social engagement of people with dementia or their carers and families in response to their stated goals or needs.Recognizing the challenges for young people and children and actively prototyping within the setting of their situation. It will require age appropriate responses and support mechanisms.

Group B participants will continue to receive usual care by health service providers and will not be denied information on dementia or dementia services in year 1. In year 2, Group B participants will have access to the “*Support for Life*” intervention making this a step-wedge study design. In year 2, Group A participants, who receive the intervention in year 1, may still access the intervention, but the intervention will no longer be actively promoted at those sites. See Figure 1 for the trial design.

**Figure 1 F1:**
[figure not shown]
**“Support for Life” stepped wedge cluster randomized control trial (SWcRCT) study design**. Overall, there are 30 clusters participating, 10 clusters in each state, and so the above figure shows the design that is replicated in each state. In each cluster, we aim to recruit 10 study participants having dementia or cognitive impairment, making the overall recruitment target at 300 participants. Data are collected from all participants during the seven data collection time points shown by a dashed-line in the above figure (i.e., at baseline and 3, 6, 12, 15, 18, and 24 months). We expect an attrition rate of 20 percent; therefore, we expect approximately 240 participants with dementia or cognitive impairment and approximately 1,680 participant data points to be examined in this SWcRCT. Attrition is expected to occur at any time point, and the modeling will include all participant data; participant data may be complete (available from all seven time points) or incomplete (available from one to six time points). The intensive intervention phase is shown in dark blue. The post-intervention phase is shown in light-blue (this is the second year for the year 1 intervention group), where participants can still access the intervention, but the intervention will no longer be promoted at those clusters.

### Outcomes

**Primary outcomes** (baseline, 3, 6, 12, 15, 18, and 24 months)*Person with dementia*
Improvement in quality of life (suitable for use by people with moderate to severe levels of dementia) (QOL-AD) (7)*Carer/family members*
Improvement in well-bein*g* of carer/family unit [Carer experience scale (CES)] (8, 9)**Secondary outcomes** (baseline, 6, 12, 18, and 24 months)*Person with dementia*
Reduction in symptoms of depression (GDS 15) (10)Increased attendance at social activities/services (staff/family/carer report/interviews)Increased engagement in social activities/services/ability to continue to participate in regular activities (staff/family/carer report/interviews)Change in health-care service utilization [client records/resource utilization in dementia (RUD) (11) health records]Delay in accessing permanent residential aged care services (client records/interviews)*Carer/family members*
Reduction in carer depression/psychological distress [General Health Questionnaire-12 (GHQ-12)] (12)Increase in social engagement and ability to continue regular activities (self report/interviews).

(See Table 1 for a full list of instruments).

**Table 1 T1:** **Outcome measures**.

	Baseline	3 months	6 months	12 months	15 months	18 months	24 months

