**Secondary outcomes**							
Person with dementia: reduced symptoms of depression	GDS 15		GDS 15			GDS 15	GDS 15
Person with dementia: increase in social activities	Interview/client records		Interview/client records	Interview/client records		Interview/client records	Interview/client records
Person with dementia: increase in social engagement	Interview/client records		Interview/client records	Interview/client records		Interview/client records	Interview/client records
Person with dementia: change in health service utilization	RUD		RUD	RUD		RUD	RUD
Person with dementia: delay in accessing permanent residential aged care services	Interview/client records		Interview/client records	Interview/client records		Interview/client records	Interview/client records
Carer/family members: reduction in depression/psychological distress	GHQ-12		GHQ-12			GHQ-12	GHQ-12
Carer/family members: increase in social engagement/ability to continue regular activities	Interview/client records		Interview/client records	Interview/client records		Interview/client records	Interview/client records

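### Sources for the attendance and engagement outcomes conflict between text and Table 1, and programme staff are not ruled out as reporters, so ascertainment may differ between intervention and control periods

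*Protocol article*

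**What the plan says.** The Outcomes section of the protocol article lists two secondary outcomes on the social life of the person with dementia. One is "Increased attendance at social activities/services (staff/family/carer report/interviews"; the other is "Increased engagement in social activities/services/ability to continue to participate in regular activities (staff/family/carer report/interviews". For carers it lists "Increase in social engagement and ability to continue regular activities (self report/interviews". Table 1, to which that section refers for the full list of instruments, gives "Interview/client records" in all three rows, at baseline, 6, 12, 18 and 24 months.

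The related secondary hypothesis is that the programme will "lead to an increase in uptake of support/respite services/engagement in activities by people with dementia in the intervention group". Uptake has no outcome line of its own. Health-service use is a separate outcome, for which Table 1 names the RUD instrument.

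The programme works directly on what is being counted. The Objectives section gives the support worker the "flexibility and autonomy to refer and link to services, assist with navigation of the service system". The Intervention section adds "Use of an assistant and volunteers to help identify/create/facilitate access to services and enhance the social engagement of people with dementia".

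On safeguards, the Blinding section says that the Research Officer who collects data is blinded. The Schedule of Events applies one data schedule to both groups. The data collection section places the interviews at the researcher's face-to-face visit.

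**The concern.** The same outcomes have two different source lists. Staff report appears only in the text, and client records appear for these outcomes only in Table 1. Neither list ranks its sources or identifies the staff or the record holder. A site could follow either list and be within the protocol.

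This matters because one possible group of reporters is present in one condition only. Support workers, assistants and volunteers are in contact with participants when the intervention is available, and they arrange the services and activities that are then counted. If their reports or notes are used, the source is richer in intervention periods, and people who know the allocation help to score the result. If bare contacts with the programme are also counted as services or activities, the outcome rises simply because the programme is being delivered. Either route could contribute to apparent support for the hypothesis on uptake and engagement.

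**Working it through.** The plan gives no figure on this point, so there is nothing to reproduce. The check sets the sections side by side and then illustrates the possible size on assumed values.

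**Sources compared**

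| Outcome | Outcomes section | Table 1 | Common to both |
|---|---|---|---|
| Attendance, person with dementia | report by staff, family or carer; interview | interview; client records | interview |
| Engagement, person with dementia | report by staff, family or carer; interview | interview; client records | interview |
| Engagement, carer | self report; interview | interview; client records | interview |

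The interview is the only source named in both places for every row.

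**Where the contrast lies.** Group A has access to the programme from year 1 and Group B from year 2. Taking Group B to cross over after its 12-month visit, the 6- and 12-month visits compare clusters with programme staff against clusters without them. After that, both groups have access.

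**What the safeguards reach.** The common schedule equalises timing. Blinding the Research Officer protects the interview. Neither changes the content of a report or record made by someone who is not blinded. The analysis plan describes how often the intervention was accessed, but the article states no rule that keeps such contacts out of the outcome.

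**Illustration 1: counts with unequal capture.** Assume 4 true activities per month in both conditions, 70% captured in control periods and 85–95% in intervention periods.
- Control: 4 × 0.70 = 2.8
- Intervention: 4 × 0.85 = 3.4, and 3.4 / 2.8 = 1.21; 4 × 0.95 = 3.8, and 3.8 / 2.8 = 1.36

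The apparent gain is 21% to 36% with no true difference.

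**Illustration 2: a yes/no outcome.** Assume true attendance p of 30% or 50% in both conditions, control capture 0.70 and intervention capture 0.75 to 0.90. The recorded proportions are a = p × control capture and b = p × intervention capture. The odds ratio is [b/(1−b)] / [a/(1−a)].
- Smallest: a = 0.30 × 0.70 = 0.21, b = 0.30 × 0.75 = 0.225, odds ratio 1.09
- Largest: a = 0.50 × 0.70 = 0.35, b = 0.50 × 0.90 = 0.45, odds ratio 1.52

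For the chance of a falsely significant benefit, take 240 / 2 = 120 per group (the plan's number after attrition) and 10 × 0.8 = 8 per cluster. With the plan's ICC of 0.05 the design effect is 1 + (8 − 1) × 0.05 = 1.35, so n = 120 / 1.35 = 88.9 per group. With p̄ = (a + b)/2, the chance is Φ{[(b − a) − 1.96 √(2p̄(1 − p̄)/n)] / √([a(1 − a) + b(1 − b)]/n)}.
- Smallest: (0.015 − 1.96 × 0.0619) / 0.0619 = −1.72, giving 4.3%
- Largest: (0.10 − 1.96 × 0.0735) / 0.0731 = −0.60, giving 27.3%

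The nominal chance in that direction is 2.5%. This is a simple two-group comparison at one visit, not the planned mixed model.

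**Illustration 3: bare programme contacts counted as activities.** Assume a base of 4 to 8 activities plus 0.5 to 2 contacts. The rate ratio is (base + contacts) / base, from (8 + 0.5) / 8 = 1.06 to (4 + 2) / 4 = 1.50.

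**The case against.** The strongest reply is that the article nowhere says that support workers, assistants or volunteers are the reporting staff, or that they keep the client records. Elsewhere the article speaks of client lists held by the community health centers. Usual care is given by health service providers, so staff and records exist in control periods too. Family or carer report and the interview are also named sources, and the interview is held on the same schedule in both groups by a researcher stated to be blinded. The article is condensed, and the full protocol may define whose reports count, the look-back period and what qualifies as an activity.

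Most of this stands, and it limits the point. A reader might infer that the programme itself generates the reports and records, so that better recording is bound to count as benefit. The document does not support that. It leaves the staff and records unidentified and does not say that programme contacts are counted. A reader might also treat attendance at an activity that the programme helped to create as an artefact. It is not: facilitating such activities is the intended effect, and the person really attends. Nor can service uptake be said to be scored from staff report, since it has no source line and health-service use is on the RUD in Table 1.

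The reply does not remove the conflict between the text and Table 1, which is on the page. A blinded collector also does not correct an unblinded source that may be fuller in one condition.

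**Conclusion.** The point holds as a conflict in the named sources and a risk of unequal ascertainment. It is not a demonstrated bias. If programme staff or volunteers contribute reports or records, the direction would probably favour the programme, but the document does not establish that it must always do so.

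The size cannot be determined from the document. The figures of 21% to 36%, odds ratios of 1.09 to 1.52 and rate ratios of 1.06 to 1.50 rest on assumed activity levels, capture rates and contact counts. They show what unequal capture would do, and are not evidence that it occurs in this trial.

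Only secondary outcomes are touched: attendance and engagement of the person with dementia, and engagement of the carer. QOL-AD and CES are not affected. For the carer row, the document does not show whether the text or Table 1 is right; it shows only that they differ.

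**What to change.** - Reconcile the Outcomes section with Table 1 for attendance and engagement, including the carer row, and state whose reports and records are meant.
- In all clusters and periods, score these outcomes primarily from the same structured interview with the person and carer, conducted by the blinded Research Officer at baseline, 6, 12, 18 and 24 months.
- Do not use reports or records made by programme staff or volunteers for these outcomes; keep them for fidelity and costing. Use other client records only if they are available in the same way in both conditions.
- Do not count bare contacts with the programme as activities or services; report them separately. Attendance at external or programme-facilitated activities still counts.

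The cost is mainly wording and a correction to the outcome text or table, since interviews are already planned at these visits. Some corroboration from records is lost, which matters in people with memory impairment. There will also be some under-reporting at interview. It may not be exactly equal between conditions, because people working with a support worker may recall or report activities differently.
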